### Analysis plan

Patients will be analyzed in the groups to which they are assigned (intention-to-treat). De-identified data (except for study number and initials) will be registered on the dedicated website requiring personal ID and password.

Study co-ordinators at the sponsor institute will perform data checks throughout the trial period and will inform participating centers if necessary.

Moreover, a monitoring committee will be provided with three visits per/year the first and second year of the study and two times per/year the third year of the study to ensure quality of data.

The primary analysis concerning QoL and PRO in both arms will be at 12 weeks, whereas 6 months and 12 months will be time points of specific interest. Standard algorithms will be used to derive scores from and handle missing data in questionnaires (IPSS, IIEF-5, EPIC-26 and EORTC-PR25). Treatment groups will be compared at individual time points and analyses to account for the longitudinal nature of the data (generalized estimating equations) may be used.

The primary analysis of freedom from biochemical/clinical progression will be event driven unless the Control Committee and Trial Steering Committees agree that the analysis performed before the target number of events is reached would be mature and robust to have the potential to influence clinical practice.

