### Endpoints of the study

#### Primary end point

Primary end point will be to determine if there is any improvement in bDFS, defined as prostate-specific antigen (PSA) rising ≥2 ng ml^−1^ over PSA Nadir, following the Phoenix criteria for biochemical recurrence of PC (after primary RT) in patients treated with prostate SRT plus ADT (ARM A) compared to patients treated with SRT alone (ARM B).

Study end points are summarized in Table 1.

**Table 1. T1:** Study end points

PRIMARY END POINTS	SECONDARY END POINTS
Determine if there is any improvement in bDFS in patients treated with prostate SRT plus ADT (ARM A) compared to patients treated with SRT alone (ARM B)	DFS FFLR FFRR FFDM OS

bDFS, biochemical disease-free survival; FFDM, freedom from distant metastasis; FFLR, freedom from local recurrence; FFRR, freedom from regional recurrence; OS, overall survival.

All biochemical failures need to be confirmed with a second PSA detection meeting the criteria for failure. In addition, it is now recognized that a benign PSA bounce may be seen in up to 20% of patients after SRT, usually within the first 2 years.^
15
^

In some cases, the magnitude of the PSA bounce may be considered as high enough for the patient to be incorrectly classified as a PSA failure. To prevent this, for patients receiving SRT, PSA failure before 24 months after the treatment will require three consecutive PSA rises to resulting a clinical diagnosis of failure, or the start of further treatment (androgen deprivation therapy). Over 24 months, the definition of PSA failure for SRT will refer to the Phoenix definition described above (*i.e.* PSA nadir+2 ng ml^−1^).

QoL and patient reported outcomes (PROs) will be an exploratory end point and will be scored with questionnaires EPIC-26, EORTC PR 25, IPSS, IIEF in SRT + ADT and SRT alone arms.

Moreover, Clinician reported Acute Toxicity, assessed with CTCAE v. 5.0 scales and Clinician reported Late Toxicity, assessed with CTCAE v. 5.0 scales will be safety end points.

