### Outcome measures and study timeline

Concerning the timing of the study, the accrual time will be 3 years and the follow-up (FU) length will be 5 years.

Patients will be screened before treatment beginning concerning performance status (PS), Testosterone, digital rectal examination (DRE), PRO (IPSS, IIEF), QoL (EPIC 26 and EORTC PR 25). Screening will exploit an online dedicated platform (www.trialspa.it). After meeting every eligibility criteria, a centralized randomization procedure will be automatically performed with a dedicated in-house software.

RT will be started within 16 weeks from randomization.

ADT will be administered form 12 weeks before RT to immediately before RT.

Evaluation will be daily performed during SRT and the last day of treatment to assess acute toxicity (CTCAE 5.0). During the last day of treatment also PRO and QoL will be scored.

Subsequently, patients will be assessed at 1 months after SRT for PS, DRE, acute toxicity, PRO and QoL.

Afterwards, 3 months after SRT completion, PSA, PS and DRE will be assessed together with toxicity PRO and QoL. For the first year of follow-up, patients will be evaluated every 3 months.

After 12 months from the end of treatment, the FU will be every 4 months. Instead, it will be scheduled every 6 months starting 24 months after the end of treatment (Figure 2).

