## Statistical considerations

### Sample size determination

In the context of normofractionated, dose-escalated PC treatment, 5 years bDFS obtained with ADT and without ADT are reported to be 84 and 69%. Due to the lack of standardized use of ADT in SRT patients, we can estimate from preliminary data on intermediate- and high risk patients a difference in bDFS of 10% at 5 years. In ARM A (SRT +ADT), we expect a bDFS of 95% at 5 years, whereas in ARM B (SRT alone), we expect a bDFS of 85% at 5 years. Considering an α error of 0,05 (2-tailed) and a 1-β of 80%, a study sample of 310 patients, 155 patients for each arm will be necessary to detect a difference of at least 10% in the two groups with a power of 83.9%.

Freedom from biochemical/clinical progression will be compared by proportions, respectively of 85 and 95% of bDFS expected in two arms, according to the sample size hypothesized above. Estimates of event rates will be calculated using the Kaplan–Meier method. The Cox proportional hazard model will be used to adjust for risk group and important known prognostic factors. Gathered data will be analyzed using SPSS^®^ v. 26.0 software (IBM^®^).

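### The arm comparisons of quality-of-life and patient-reported scores state no use of the baseline scores already collected; adjusting for them would be a minor, cost-free gain in precision on an exploratory end point

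*Protocol article*

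**What the plan says.** The Analysis plan sets the main time point: "The primary analysis concerning QoL and PRO in both arms will be at 12 weeks". Six and 12 months are named as further time points of interest. On method it says: "Treatment groups will be compared at individual time points". The same sentence allows a longitudinal analysis but does not require it. The visit-by-visit comparison is therefore a commitment and the generalised estimating equations (GEE) are an option. No test, model or covariate is named for either.

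The section Outcome measures and study timeline lists, among the screening assessments, "PRO (IPSS, IIEF), QoL (EPIC 26 and EORTC PR 25"). Screening comes before the central randomisation, and the caption of Figure 2 also describes these questionnaires as assessed before randomisation.

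The section on the primary end point gives the status of these outcomes: "QoL and patient reported outcomes (PROs) will be an exploratory end point".

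Covariate adjustment is stated in one place, under Sample size determination, for the efficacy analysis: "The Cox proportional hazard model will be used to adjust for risk group and important known prognostic factors". Nothing equivalent is said for the questionnaires.

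**The concern.** A score at 12 weeks reflects both treatment and the man's urinary, bowel or sexual function before treatment. A comparison of follow-up scores alone leaves the second part in the error term. Minimisation balances age group and risk group only, so baseline function can still differ between arms by chance.

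Precision matters here for two reasons. The sample size was set for biochemical disease-free survival (bDFS), and no SD, effect size or power is given for any questionnaire, so precision on these scales depends on the number of men available and the method of analysis. The article also gives these results a visible role. The Abstract expects them, with acute toxicity, 6 months after the last patient enters, whereas efficacy follows at 3 to 5 years. The Discussion relies on them for early information on the tolerability of the combination.

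**Working it through.** **The plan's own figure.** The only stated power is 83.9%, for bDFS of 85% against 95% with 155 per arm and two-sided α of 0.05 (Sample size determination). With the pooled-variance normal approximation:

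- Standard error under no difference: √(2 × 0.90 × 0.10 / 155) = 0.03408.
- Standard error under the alternative: √((0.85 × 0.15 + 0.95 × 0.05) / 155) = 0.03360.
- Power: Φ((0.10 − 1.96 × 0.03408) / 0.03360) = Φ(0.988) = 83.85%.

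This reproduces the stated 83.9%. It concerns the primary end point and does not bear on the questionnaires.

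**Inputs for the questionnaire contrasts.** From the article: 155 per arm and 1:1 allocation. The 5% two-sided level and 80% power are borrowed from the bDFS calculation as a yardstick. Assumed: the correlation r between baseline and follow-up score (0.3 to 0.7, because the article gives none), equal variance in both arms, and all 155 men per arm assessed.

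**Unadjusted contrast at one visit.** The detectable difference is (1.960 + 0.842) × √(2/155) = 2.8016 × 0.11359 = 0.318 SD.

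**Contrast adjusted for baseline.** The residual variance is (1 − r²) times the unadjusted variance. Hence:

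- detectable difference = 0.318 × √(1 − r²);
- power for a true difference of 0.318 SD = Φ(2.8016/√(1 − r²) − 1.960);
- men per arm that match 155 unadjusted = 155 × (1 − r²), rounded up.

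| Assumed r | Variance cut | Standard error ratio | Detectable difference (SD) | Power at 0.318 SD | Matching n per arm |
|---|---|---|---|---|---|
| none (unadjusted) | – | 1.000 | 0.318 | 80% | 155 |
| 0.3 | 9% | 0.954 | 0.304 | 83.6% | 142 |
| 0.4 | 16% | 0.917 | 0.292 | 86.4% | 131 |
| 0.5 | 25% | 0.866 | 0.276 | 89.9% | 117 |
| 0.6 | 36% | 0.800 | 0.255 | 93.8% | 100 |
| 0.7 | 49% | 0.714 | 0.227 | 97.5% | 80 |

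Missing questionnaires would raise the detectable differences, but the ratio √(1 − r²) depends on r alone.

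**Change scores are not a substitute.** A simple comparison of change from baseline has a standard error of √(2(1 − r)) times the unadjusted one: 1.18 at r = 0.3, 1.00 at r = 0.5 and 0.77 at r = 0.7. It loses precision below r = 0.5, and at each of these values it is worse than adjustment.

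**The case against.** The strongest case against is that the article is silent on adjustment and does not reject it. An ANCOVA at 12 weeks is itself a comparison at an individual time point, so the text is compatible with the method recommended here. The article is condensed, and the covariates for an exploratory questionnaire analysis are often left to the full protocol or statistical analysis plan, neither of which is shown. This largely stands. A reader might infer that the plan discards baseline, and the text does not support that. What remains is that the article does fix part of the method: it commits to separate time points, makes the longitudinal model optional, and names adjustment for efficacy only.

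Three other stronger readings also fail.

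- A reader might infer that the unadjusted contrasts are biased. Under randomisation they are not, and their intervals already allow for chance imbalance.
- A reader might infer that most of the variance is already present before treatment. Even at r = 0.7 baseline explains 49%. The IPSS limit of 0 to 15 is an eligibility cap, which narrows the baseline spread on that scale and may lower its r.
- A reader might infer that the tolerability assessment depends on these contrasts. Clinician-reported CTCAE toxicity is the safety end point, has its own tests, and its acute part reads out at the same time.

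The size of the gain rests wholly on the assumed r. If treatment drives sexual scores towards the floor in the androgen-deprivation arm, r on that domain could be low and the gain small.

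**Conclusion.** The point holds as a minor one. As written, the commitment is to comparisons at single time points with no stated use of baseline scores that are already collected. If carried out unadjusted, they are valid but less precise than they need be. For r between 0.3 and 0.7, adjustment shortens the standard error by 5% to 29%. There is some gain for any non-zero r, but the article contains nothing that fixes r, so no single figure should be quoted as the loss. The outcomes are exploratory, and nothing here touches the primary end point, the 310 patients or the 83.9% power.

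**What to change.** Add one sentence to the Analysis plan: the 12-week (main), 6-month and 12-month comparisons of each scale adjust for the baseline score of that scale and for the two minimisation factors, age group and risk group.

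ANCOVA at each visit is enough. One repeated-measures mixed model per scale is preferable, with arm, visit, arm-by-visit, baseline score and the minimisation factors, and all three contrasts read from the same model. It uses every available visit and stays valid if missed questionnaires depend on observed scores. Standard unweighted GEE needs them to be missing completely at random. The article gives no dropout figure, so this is a reason for preference only. If the full protocol or statistical analysis plan already specifies baseline adjustment, it is enough to bring the article's wording into line.

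The cost is a sentence of text and slightly more analysis work. No new data, visits or patients are needed.

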**Results::**

Sample size is estimated of 310 pts. For acute toxicity and quality of life results are awaited after 6 months since last patient in, whereas, for efficacy end points and late toxicity mature results will be available 3–5 years after last patient in.

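### The primary analysis is timed by an event target that the fixed 5-year sizing does not supply, and it may be advanced on a criterion not tied to blinded information, so control of the 5% level is not assured

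*Protocol article*

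**What the plan says.** Three parts of the article bear on when the primary comparison is made.

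- **Sample size determination.** The assumptions are fixed-time proportions: "In ARM A (SRT +ADT), we expect a bDFS of 95% at 5 years" and "in ARM B (SRT alone), we expect a bDFS of 85% at 5 years". From these, "Considering an α error of 0,05 (2-tailed) and a 1-β of 80%, a study sample of 310 patients, 155 patients for each arm" is derived, with a stated power of 83.9%. The same section says the arms will be compared by proportions. Kaplan–Meier estimates and an adjusted Cox model are mentioned alongside.
- **Analysis plan.** The primary analysis is to be event driven, with one exception: "unless the Control Committee and Trial Steering Committees agree that the analysis performed before the target number of events is reached would be mature". The early analysis must further be robust, and it must "have the potential to influence clinical practice". The article gives no figure for the target.
- **Abstract, Results.** For efficacy and late toxicity, "mature results will be available 3–5 years after last patient in".

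The trial is open label, with 3 years of accrual and a follow-up length of 5 years. An interim analysis at 50% accrual is planned to check the design assumptions. The sample size is re-estimated if interim results differ from them by more than 15%. The only error rate stated is 0.05, two-tailed.

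**The concern.** There are two linked problems.

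First, the timing rule and the sizing belong to different designs. A comparison of 5-year proportions is due when patients reach 5 years. An event-driven analysis is due when a count is reached, whenever that is. The rule for an early analysis is defined relative to that count, and the sizing does not produce one. Without it, nobody could later show whether an analysis was early.

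Second, the exception turns partly on whether the result could influence practice. Maturity and robustness can be judged from pooled data. Influence on practice is hard to judge without some idea of the difference between arms, and nothing in the clause restricts the committees to blinded information. If the date follows a favourable difference, the false-positive rate rises and the estimated effect at that date tends to be exaggerated. This would touch the one confirmatory test of a trial that aims to set a standard of care.

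**Working it through.** **1. Reproduce the plan's power.** Inputs from the sample size section: n = 155 per arm, p = 0.85 and 0.95, two-sided α = 0.05. Pooled variance, no continuity correction:

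- SE under the null = √(2 × 0.90 × 0.10 / 155) = 0.03408
- SE under the alternative = √((0.85 × 0.15 + 0.95 × 0.05) / 155) = 0.03360
- Power = Φ((0.10 − 1.96 × 0.03408) / 0.03360) = Φ(0.988) = 83.85%, against 83.9% stated

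The figure reproduces. No event count enters the formula and none comes out of it.

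**2. Events that the design rates imply by 5 years.** 155 × 0.15 + 155 × 0.05 = 23.25 + 7.75 = 31, if every patient is followed for exactly 5 years with no dropout.

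**3. Event target if the design were event driven** (proportional hazards assumed).

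- HR = ln 0.95 / ln 0.85 = 0.316
- Schoenfeld, 83.9% power: 4 × (1.96 + 0.99)² / (ln 0.316)² = 26.2, so 27 events
- Freedman, 83.9% power: (1.96 + 0.99)² × ((1 + 0.316) / (1 − 0.316))² = 32.2, so 33 events
- For 80% power: 24 (Schoenfeld) or 30 (Freedman)

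A target anywhere in 24–33 is thus compatible with the stated assumptions. Its upper end exceeds the 31 events expected under 5 years of follow-up per patient. If early patients are instead followed for up to 8 years (uniform 3-year accrual, exponential hazards, no dropout), about 28 events are expected 3 years after the last patient enters and about 39 at 5 years. So whether a given target can be reached depends on how the follow-up length is read.

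**4. Type I error.** With one test at a time chosen without knowledge of the effect, it is 5.0%. With two tests, each at two-sided 5%, it is 1 − P(|Z₁| < 1.96 and |Z₂| < 1.96), where corr(Z₁, Z₂) = √f and f is the information fraction at the early test. The article gives no f, so a range is shown:

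| f (assumed) | Type I error |
|---|---|
| 0.50 | 8.3% |
| 0.60 | 8.0% |
| 0.75 | 7.3% |
| 0.90 | 6.5% |

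**5. Levels that would hold 5% overall.** Lan–DeMets O'Brien–Fleming-type spending, two-sided levels for the early and final test: 0.0031 and 0.0490 at f = 0.50; 0.0076 and 0.0476 at f = 0.60; 0.0193 and 0.0442 at f = 0.75.

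**The case against.** The strongest reply is that the Analysis plan speaks of one primary analysis whose date may move. Moving the date of a single test does not by itself raise the error rate. The clause also requires that the analysis be mature and robust and that both committees agree. Open label means treatment is known patient by patient; it does not mean that the committees hold pooled comparative data. The article is condensed, and an event target, a boundary or rules on committee access may stand in the full protocol or SAP.

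Most of this stands, and it rules out several stronger readings.

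- A reader might infer that the 5% level is already lost. The article describes neither a repeated test nor a decision informed by the treatment difference, so it shows only that control is not assured.
- A reader might take the abstract's 3–5 year window as a schedule of full-level tests. Tests at about 28 and 39 events would give roughly 7.5%, but the window states when results are expected and also covers late toxicity.
- A reader might count the 50%-accrual interim as a further efficacy test. Its stated aim is to check the assumptions. Only about 2.5 events are expected then (uniform accrual, exponential hazards), and even a 3–0 split gives z = 1.5 / √0.75 = 1.73, below 1.96.
- The absence of a target figure from the article does not prove that none exists.

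The reply does not remove the conflict between a fixed 5-year comparison and event-driven timing. Both are stated in the article. Nor does it change the criterion as written, which rests partly on influence on practice and is not restricted to blinded information.

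**Conclusion.** The point holds as a badly fixed rule. The article gives two incompatible bases for the time of the primary analysis, and its sizing, though arithmetically sound, cannot supply the event target that the timing rule needs. The exception allows a decision informed by the effect without requiring one, so the two-sided 5% level is not assured.

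The size depends on how the clause is used: no inflation with one test timed blind to the effect, and about 6.5–8.3% with an early and a later test, both unadjusted. The second range rests on assumed information fractions of 0.50–0.90 and on a second test that the article does not describe. The implied 27–33 events for 83.9% power rest on proportional hazards at the design rates.

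**What to change.** 1. **State one analysis time that matches the sizing:** a single primary analysis when all patients have completed 5 years of follow-up, at two-sided α = 0.05, with about 31 events expected by 5 years under the design rates. Bring the abstract's 3–5 year statement into line.
2. **If event-driven timing is preferred,** base the primary test and the power on a log-rank or Cox analysis and state a target that the follow-up can deliver. A bare count of 33 would not do: it exceeds the 31 events expected with 5 years of follow-up per patient, and a log-rank count does not govern a comparison of proportions.
3. **Settle the exception** in one of three ways:
   - delete it;
   - limit it to a decision made blind to the treatment comparison, with one test only; or
   - prespecify O'Brien–Fleming-type spending (for example about 0.019 early and 0.044 final at 75% information), with comparative data seen only by an independent committee.
4. **State that the 50%-accrual interim makes no efficacy test.**

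This is a change of wording and needs no more patients. The price is that an early report is given up or must meet a stricter threshold. The change should be made before anyone sees comparative outcome data, because a timing rule chosen afterwards would carry little weight.

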### Interim analysis

Due to the lack of data in the context of ADT combined with prostate SRT for the treatment of PC, an interim analysis after a 50% accrual of sample size will be planned. The aim of this procedure will be to verify the subsistence of the previously reported statistical hypothesis. A sample size re-estimation will be performed in case interim results will differ from our estimates more than 15%.

## Discussion

In the context of localized PC, the evidence of a safe, effective and more convenient treatment will move the clinical and patient’s choice toward SRT. Advances in image guidance such as MRI-guided RT is a promising approach to increase the therapeutic index in this context.^
16
^ Remarkably, several recent studies, including clinical trials, have tested SRT efficacy on localized PC omitting ADT.^
5–7,15,17
^

Of note, ADT is widely recognized to improve outcomes in combination with standard and moderate fractionated RT for a subclass of intermediate- and high risk PC patients. Biological rationale of combining RT and ADT were reported in literature,^
10
^ although the role of ADT in the context of high dose-per-fraction schedule is still uncertain.^
18
^ Therefore, ADT effect in combination with normofractionated and hypofractionated RT is not clearly movable to ultra-hypofractionation.^
8,9
^

Recently, in high risk patients, the SHARP consortium prospectively evaluated 344 treated patients, with the aim to explore the efficacy and toxicity of SRT in the context of high risk PC. 72% of patients received ADT (investigator’s choice), with a median duration of 9 months. At univariate analysis, 4 years bRFS resulted significantly greater among patients treated with concurrent ADT but 4 years DMFS was not significantly different.^
11
^ Given the non-randomized nature of the studies included, selection bias may have influenced the choice to administer ADT. As a consequence, such variable did not enter in multivariable model. Differently, Jackson et al in a meta-analysis of over 6000 pts treated on prospective studies did not found any advantage for ADT use on bDFS, Remarkably, in both studies, ADT use was administered at investigator’s choice and therefore caution must be exercised in the interpretation of these results.

Regarding toxicity, multivariable logistic regression for acute and late toxicity showed that ADT use and 8 Gy per-fraction schedule were associated with higher risk of GU Grade ≥ 3. The physiopathogenesis of increased toxicity with ADT use is unclear. One of the hypothesis concerning both GU and gastrointestinal (GI) side-effects consists in the possible downstaging and shrinking effect determined by ADT that could contribute to an higher than expected dose to critical organs such as bladder and rectum.^
11,19
^

The optimal dose for prostate SRT is still unknown. Levin-Epstein et al retrospectively compared crude biochemical control, bRFS and ablation rate of four different ultra-hypofractionated schedules in 1908 men. Authors show a hypothesis of superiority of 40 Gy in 5 fractions in terms of crude biochemical recurrence. Interestingly, this study showed no difference in terms of 5 years bRFS, and all the schedules obtained brilliant results in term of bRFS (all showing at least 93% bRFS probability at 5 years, without ADT). Moreover, no data on local control and toxicity were reported.^
20
^

Concern about the limited therapeutic window of prostate SRT was suggested also by a systematic review and meta-analysis of 6000 pts, where an impact on bRFS of more aggressive schedule was proposed, but a significantly increase in GU Grade ≥ 3 toxicity was also registered. 36,25 Gy in 5 fractions showed similar GU and GI toxicity rates compared to moderately hypofractionated RT.^
5
^ In terms of efficacy, available studies reported excellent bRFS rates, also without ADT, in unfavorable intermediate and high risk pts.^
11,20
^

Given these hypotheses and the lack of high quality randomized data directly testing the eventual superiority of a specific SRT regimen, 36.25 Gy in 5 fractions has been the schedule of choice for our trial.

In this scenario, clarification of the contribution of ADT in addition to prostate SRT is clearly needed. We are confident that the present multi-institutional, randomized-controlled trial will provide clinicians with reliable evidence to support treatment decisions. The primary analysis of QoL in both arms will be at 12 weeks, whereas 6 months and 12 months will be time points of specific interest, allowing to obtain in a relatively short time valuable information regarding the tolerability of the SRT + ADT association. The main limitation of the study is that the statistical hypotheses of the expected difference in bDFS between the two groups could be rejected, due to the lack of data in this context (as this is still an unexplored scenario). For this reason, an interim analysis after an accrual of 50% of the expected patients has been planned, and then a sample size re-estimation will be performed whether interim results differ from our estimates by more than 15%. Another limitation of this trial, is the possibility to use both prostate-specific membrane antigen (PSMA)-PET/CT and conventional imaging (99mTc bone scan and CT scan) for the initial staging of disease. Recent publications reported a higher accuracy of PSMA-PET/CT than conventional imaging in the initial staging assessment of males with newly diagnosed, high risk PC. In fact, PSMA-PET/CT has proven to have higher specificity and positive-predictive value in detecting sites of disease that are not visible in conventional imaging.^
21,22
^ Such findings may suggest the potential creation of two further subgroups in our study: patients with non-metastatic, high risk PC submitted to conventional staging of disease, and patients with non-metastatic, PSMA-negative, high risk PC. A post-hoc subgroup analysis of these two cohorts of patients could demonstrate the possible clinical implication of these two different staging modalities, and further clarify the impact of next-generation imaging in the management of high risk PC.

